### Measures

• *The Structured Clinical Interview for DSM-IV-Axis I and II *(SCID-I and II) [31,32]: is a semi-structured interview that allows for the diagnosis of Axis I and II disorders, respectively, according to DSM-IV criteria [1].

• *The Clinician-Administered PTSD Scale *(CAPS) [33]: is a structured interview developed to diagnose PTSD and rate its severity. It is comprised of 30-items to assess PTSD-related symptom frequency and severity. Scores range from 0 to 136, with scores classified as follows: subclinical, from 0 to 19; mild, from 20 to 39; moderate, from 40 to 59; severe, from 60 to 79; extreme, 80 and above.

• *The Beck Depression Inventory *(BDI) [34]: is a 21-item self-report inventory designed to measure the severity of depression. Scores range from 0 to 63, with depression classified as minimal when scores range from 0 to 11, mild from 12 to 19, moderate from 20 to 35, and severe from 36 to 63.

• *MOS 36-Item Short-Form Health Survey *(SF-36) [35]: is a scale to measure mental and physical health concepts. It is a 36-item self-report instrument. The SF- 36 measures social functioning correlated to clinical conditions. As higher is the score, better is the quality of life. The instrument gave a global score, as specific areas scores: functional capacity, physical aspects, pain, general health condition, vitality, social aspects and emotional aspects, and mental health.

• *Social Adjustment Scale *(SAS) [37]: is a 54-item scale, ranging from 1 to 5 from normal to severely misadjusted. Used to evaluate social adjustment, normal score is around 1.56 (+/- .36).

• *Global Assessment of Functioning (GAF) Scale *[38]: is a single-item rating scale for evaluation the overall patient functioning during a specified period on a continuum from psychological or psychiatric sickness to health. The scale value ranges from 1 (hypothetically sickest person) to 100 (hypothetically healthiest person), divided into 10 equal intervals. A modified version of the Global Assessment Scale (GAS) was included in DSM-III as the Global Assessment of Functioning (GAF) Scale.

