### Sample Size

The number of subjects calculated for the trial is 72, being 36 on each cell. The sample size was calculated considering a 5% probability of type I error (significance level), and 20% for type II error (power test of 80%), on a bi-caudal test. To the calculation we use an average of 60% for response from PTSD for active drugs, based on published literature, and 30% of placebo response.

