### Statistical Analysis

All data will be analyzed by SPSS (version 13.0). The frequencies of nominal variables from all patients will be calculated. The data analysis will be conducted using a ANOVA comparing each scale during the 2 continuous measures from baseline and 12 weeks with a Between Subject factor was included as independent variable (treatment group). The confidence level that will be used for all comparisons will be 5% (p < .05). All observed Power as a type II error function will be presented with minimum values of significance for each comparison. CAPS scores from baseline and endpoint will be stratified according severity, as nominal data they will be compared using the chi-square test and the Fisher test when there were cells that counted less than five or at least one cell counted zero subjects. For missing data we will use the last observation carried forward strategy for an intention-to-treat analysis.

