Efficacy analyses will be performed in the intent-to-treat population of patients who received at least one dose of topiramate. The primary efficacy endpoint will be the change in PTSD Scale- CAPS total score from baseline to the final visit at 12 weeks, which will be compared between treatment groups. Missing efficacy data at 12 weeks will be imputed with the last observation carried forward. The secondary outcomes between groups will be comparing the Clinical Global Impressions (CGI), the Beck Depression Inventory (BDI), the Global Assessment of Function (GAF), and the PANAS scales. Other secondary analyses will include an evaluation after 24-weeks (12-week after last patient visit with drug) data with endpoint analyses between the treatment groups covarying for baseline scores. On all secondary outcomes, the Bonferroni correction will be applied for testing multiple variables. Response will be defined as a 20% improvement in the baseline CAPS total or positive symptom scores at 12 weeks and will be compared between treatment groups using a chi-square test. Proportions of patients completing the 12-week double-blind study will be compared between treatment groups using a chi-square test. Adverse events reported by 10% of patients in each treatment group will be compared using a chi-square test. Laboratory values, vital signs and physical examinations are going to be compared from baseline and in reference to normal ranges, and reported as normal or abnormal. Changes in body weight (lb), body mass index (BMI; kg/m2) at last visit in the 12-week dataset will be compared as mean changes between treatment groups using t-tests.

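### The CAPS severity bands are ordered but tested as nominal data, which costs about 15 to 22 points of power in a supplementary comparison

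*Protocol article*

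**What the plan says.** The Measures section of the protocol article divides the CAPS total (0 to 136) into five bands: "subclinical, from 0 to 19; mild, from 20 to 39; moderate, from 40 to 59; severe, from 60 to 79; extreme, 80 and above". This is the only severity classification of CAPS in the document.

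Under Statistical Analysis, "CAPS scores from baseline and endpoint will be stratified according severity", and "as nominal data they will be compared using the chi-square test". The alternative is "the Fisher test when there were cells that counted less than five or at least one cell counted zero subjects". No trend, rank or ordinal-model test of the bands is named.

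The band comparison stands beside the main analysis. The same section states: "The primary efficacy endpoint will be the change in PTSD Scale- CAPS total score from baseline" to the 12-week visit. It also plans an ANOVA of each scale and a chi-square comparison of responders. The bands do not appear in its list of secondary outcomes.

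On size, the Sample Size section says: "The number of subjects calculated for the trial is 72, being 36 on each cell". It assumes 60% response on active drug and 30% on placebo, with a two-sided 5% level. No power is stated for the band comparison.

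**The concern.** Severity bands are ordinal. The document assigns them the wrong data type and then picks a test to match. This is not a detail left to a fuller plan, because the data type, the test and the switching rule are all written down.

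The trial asks whether topiramate moves patients towards lower severity. A general chi-square or Fisher test of two arms by five bands treats every difference in pattern alike. It spreads its sensitivity over 4 degrees of freedom, when the question of interest is a shift in one direction. It can therefore miss a consistent move to milder bands. It can also reach significance for a difference that favours neither arm. What is at stake is the power and readability of this one comparison.

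**Working it through.** The document gives no power for the band test, so there is no stated figure to reproduce. The check compares the nominal test with an order-using test on the same bands.

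**Inputs from the protocol article**
- 36 per arm, two-sided 5% level, 60% versus 30% response (Sample Size).
- Band limits at 20, 40, 60 and 80 (Measures).
- CAPS differences (Background): 52.7 − 42.0 = 10.7 points in the 38-patient topiramate monotherapy trial (p = .232), and 5.76 points in the pooled medication trials.

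**Assumptions, because the document does not give them**
- The strata are the five Measures bands, compared between arms in a 2 × 5 table with (2 − 1)(5 − 1) = 4 degrees of freedom.
- SD 27. This is back-calculated from the 38-patient trial, assuming 19 per arm and an unadjusted t-test. For p = .232 on 36 df, t = 1.216, so SE = 10.7/1.216 = 8.8 and SD = 8.8/√(2/19) = 27.1. This is an SD of change, used here as a stand-in for the SD of week-12 scores, so SDs of 20 to 30 were also run.
- Placebo means of 40 to 60 at week 12.

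**Step 1: cost of the extra degrees of freedom.** Take a shift whose noncentrality gives a stated power on 1 df, and test it on 4 df:

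| Power on 1 df | Power on 4 df |
|---|---|
| 30% | 18% |
| 50% | 31% |
| 80% | 59.5% |
| 90% | 74% |

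**Step 2: the planning effect.** The odds ratio for 60% versus 30% is (0.6/0.4)/(0.3/0.7) = 1.5/0.4286 = 3.5. This was applied as a proportional-odds shift across the five bands, for four different placebo distributions (20,000 simulated trials each). The nominal chi-square has 58–62% power and the Wilcoxon test on the bands 80–83%, a loss of about 21 to 22 points. At odds ratio 2 the figures are 20–21% and 36–37%. At odds ratio 5 they are 81–85% and 95–96%.

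**Step 3: CAPS-point differences.** Normal scores, cut into the bands, SD 27, placebo mean 40 or 50:

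| Difference | Nominal chi-square | Wilcoxon on bands |
|---|---|---|
| 10.7 | about 18% | about 34% |
| 15 | 34–38% | 58–60% |
| 20 (mean 50) | about 62% | about 83% |

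**Step 4: sensitivity to the SD.** At 10.7 points and placebo mean 50, SD 20 gives 32% versus 56% (24 points lost) and SD 30 gives 16% versus 29% (13 points lost). Over all the SDs and means at 10.7 points, the nominal test keeps 53–60% of the ordered test's power. At 5.76 points it keeps 51–66%, with both tests weak (8–11% versus 12–21%). At 20 to 25 points it keeps 67–99%.

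**Step 5: type I error.** With no difference between arms, both tests stay close to 5% (4.3% nominal and 4.8% ranked in one run at SD 27). The gain in power is not bought with extra false positives.

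**The case against.** The strongest objection is that little depends on this test. The primary analysis uses the continuous CAPS total, which already captures an ordered shift. In simulation with SD 27, a t-test on the continuous scores had 38% power at 10.7 points and 60–64% at 15. The Wilcoxon test on the bands had 35% and 57–60%. This stands, and it sets the weight of the point: an improvement to a supplementary comparison.

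The table itself is also partly inferred. The Statistical Analysis section does not say that its strata are the five Measures bands, or that arms are compared rather than baseline with endpoint. Fewer strata would change the degrees of freedom and the power figures. A within-patient comparison would call for a different test altogether, since an ordinary chi-square does not suit paired data. This stands too, so the figures are conditional.

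Three stronger readings are tempting, and the document does not support them.
- *The nominal test roughly halves the power.* That is near the truth only for small to moderate differences, where the ordered test is weak as well. At the planning effect the loss is about a quarter of the power, and it shrinks as effects grow. The document gives no SD or band distribution from which a general halving could be derived.
- *The switch to Fisher's test does harm.* Tying it to observed rather than expected counts is poor practice. With ten cells and 72 patients, at least one cell fell below five in about 99% of simulated trials with an effect, so the exact test would nearly always apply. But that test is valid, and its power is close to the chi-square's: 19–21% at 10.7 points, 34–38% at 15 and 61% at 20. No damage is shown.
- *The trial could miss its main effect because of this.* The primary endpoint does not pass through the band table.

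**Conclusion.** The point holds in a limited form. The document labels ordered severity strata nominal and names tests that ignore the order. If the five bands are compared between arms with 36 each, the cost against a consistent shift is about 15 to 22 points of power in the two reference scenarios: about 18% versus 34% at 10.7 points with SD 27, and about 60% versus 80% at odds ratio 3.5. The first scenario rests on an assumed SD and assumed placebo means. The second rests on carrying the response odds ratio over to the bands. The direction of the loss is the same throughout, and its size depends on the scenario.

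Nothing is biased or invalid, and the primary conclusion is unaffected. The change is worth making because it is almost free.

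**What to change.** In Statistical Analysis, replace the nominal comparison of CAPS strata with one sentence. It should say that the five bands defined under Measures will be compared between arms at week 12 with a method that uses their order: Wilcoxon rank-sum, linear-by-linear trend, or a proportional-odds model adjusted for baseline CAPS. Name one of these in advance. The sentence also settles which strata and which comparison are meant. The chi-square/Fisher switching rule can then be dropped for this comparison.

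The cost is one sentence of wording. It needs no new data or patients, and the methods are standard.

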#### Active treatment phase

Those patients without improvement during the placebo trial, and do not show any laboratory and clinical condition exclusion criteria will be randomly assigned to receive either placebo or topiramate, in a 1:1 ratio using computer- generated code. The active and placebo pills will be identical. All research and clinical staff will be blinded to the randomized assignments.

Study medication will start at 25 mg/day once daily, at night, and will be increased 25 mg weekly, as tolerated, until complete or nearly complete efficacy is achieved or until 200 mg/day is reached. No other psychotropic medications will be allowed during the study, except for zolpidem (10 mg/day), if needed, for insomnia.

Study follow-up visits will be conducted at baseline, and weeks 1, 2, 3, 4, 6, 8, and 12.

Symptoms and side effects will be assessed, as well as measurement of systemic blood pressure and pulse rate in each visit by the investigator, who is blind to medication assignment. Compliance will be assessed by counting the amount of pills left in the bottle of medicine in each visit.

Treatment will be continued for 12 weeks (active treatment phase); then drug administration will be withdrawn gradually during 2 weeks with reductions of 25/50 mg every three days, according to the final dosage reached.

Patients will be assessed until completing 6 months during a follow-up period. If a patient showed a symptomatology worsening during the active treatment phase (12 weeks) when receiving active drug treatment, characterized by a one-point decrease at CGI -I or present serious adverse effects related to medication, he/she will be excluded from the study.

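### The last-observation-carried-forward rule has no time limit, so it can put on-treatment scores into the off-drug 24-week comparison

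*Protocol article*

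**What the plan says.** The first paragraph of Statistical Analysis describes an "ANOVA comparing each scale during the 2 continuous measures from baseline and 12 weeks" and closes with the general rule: "For missing data we will use the last observation carried forward strategy for an intention-to-treat analysis". No time point is attached to that rule.

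The second paragraph places the efficacy analyses in the intention-to-treat population. After defining the primary endpoint it adds: "Missing efficacy data at 12 weeks will be imputed with the last observation carried forward". It then plans a later comparison: "Other secondary analyses will include an evaluation after 24-weeks (12-week after last patient visit with drug) data with endpoint analyses between the treatment groups", adjusted for baseline scores. No missing-data method is given for that comparison.

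The Active treatment phase section fixes the treatment state at each time. After 12 weeks of treatment, "then drug administration will be withdrawn gradually during 2 weeks". The visit schedule stops at the end of treatment: "Study follow-up visits will be conducted at baseline, and weeks 1, 2, 3, 4, 6, 8, and 12". Beyond that the text says only: "Patients will be assessed until completing 6 months during a follow-up period". No assessment weeks between 12 and 24 are listed.

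**The concern.** The 24-week analysis can answer one question: does any difference between the arms persist once the drug has been withdrawn? A score taken on topiramate does not measure that state. The general rule, read as written, nevertheless supplies such a score whenever a topiramate patient has no rating after week 12.

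This differs from the usual objection to carry-forward, which turns on informative dropout. Here the carried value comes from a different treatment state, so the estimate is biased even when 24-week visits are missed completely at random. If the effect fades off drug, each imputed topiramate patient pulls the 24-week difference back towards the on-drug difference. The report could then describe a lost effect as partly maintained.

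**Working it through.** **Treatment state at week 24.** Treatment ends at week 12 and the taper takes 2 weeks, so drug exposure ends at about week 14. Week 24 is then about 24 - 14 = 10 weeks after the last dose.

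**Which score is carried.** Under the unrestricted rule:
- a topiramate patient rated at week 12 and not afterwards carries the on-drug week-12 score;
- a topiramate patient who stopped earlier carries an earlier score, possibly baseline;
- a patient with an unscheduled or unlisted rating between weeks 12 and 24 carries that rating;
- a placebo patient carries a placebo score, which involves no change of drug state.

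The first group is the clearest case and the one sized below.

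**Bias formula.** Let m be the share imputed in each arm, d12 the week-12 effect and d24 the true week-24 effect. With random missingness the carried-forward estimate has mean (1 - m) x d24 + m x d12, so

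bias = m x (d12 - d24).

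If the shares differ by arm and placebo scores are stable from week 12 to week 24, m is the topiramate share.

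**Inputs.** The plan gives no figure for the 24-week analysis, so there is none to reproduce. The 24-week sentence does not name a scale; CAPS total is assumed here.
- d12 = 5.76 points: the pooled medication-placebo difference cited in Background.
- d12 = 52.7 - 42.0 = 10.7 points: the earlier 38-patient topiramate monotherapy trial cited in Background (p = .232).
- d24 = 0: assumed (effect fully lost).
- m = 10% to 40%: assumed; the document states no expected loss at week 24.
- 36 per arm: Sample Size section.

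| Share imputed | d12 = 5.76 | d12 = 10.7 |
|---|---|---|
| 10% | 0.6 | 1.1 |
| 20% | 1.2 | 2.1 |
| 30% | 1.7 | 3.2 |
| 40% | 2.3 | 4.3 |

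**Scale against sampling error.** Assuming 19 per arm in the earlier trial, p = .232 gives t of about 1.215 on 36 degrees of freedom. Then SE = 10.7 / 1.215 = 8.8, and SD = 8.8 / sqrt(2/19) = 27.1. At 36 per arm, SE = 27.1 x sqrt(2/36) = 6.4. At 30-40% imputed the bias is:
- d12 = 5.76: 1.7/6.4 to 2.3/6.4, or 0.27 to 0.36 SE;
- d12 = 10.7: 3.2/6.4 to 4.3/6.4, or 0.50 to 0.67 SE.

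**Effect on a two-sided 5% test** (the level in Sample Size), with a shift of b standard errors: rejection rate = Phi(-1.96 + b) + Phi(-1.96 - b). For b = 0.50 this is about 7.9%, and for b = 0.67 about 10.3%. A simulation of the 10.7-point case (36 per arm, SD 27.1, assumed correlation 0.6 between weeks 12 and 24, 4000 runs per rate) agrees. At 10%, 20%, 30% and 40% missing, the carried-forward mean difference was -1.1, -2.2, -3.3 and -4.3, with rejection rates of 5.2%, 6.2%, 7.6% and 10.1%. Using observed week-24 scores alone, the mean difference was about 0 and the rejection rate 4.9-5.5%.

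**The case against.** **No contradiction.** A reader might infer that the second paragraph confines carry-forward to week 12 and so conflicts with the first. It does not. The week-12 sentence follows the primary endpoint and applies the general rule to it; nothing in it excludes other times. The two sentences are compatible.

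**No planned completer analysis.** A reader might also infer that the 24-week analysis would otherwise be run on completers only. The document plans no such analysis.

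**The rule may have been meant for week 12 only.** It closes a paragraph whose named model uses baseline and week 12. On that reading the article has no 24-week rule, and that absence alone would be no finding, because such detail is commonly left to a fuller document. The reading is possible, but the sentence is not worded that way, and the efficacy analyses, of which the 24-week comparison is one, are placed in the intention-to-treat population the rule serves. The point rests on a stated rule that is wrong for a planned analysis, not on an omission.

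**Not every gap is filled with an on-drug week-12 score.** Early dropouts, placebo patients and anyone rated between weeks 12 and 24 carry something else. This stands and limits the size.

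**The size is assumption-driven.** The 10.7-point effect comes from a small, non-significant trial, and full loss of effect is the extreme case. The cited 16 of 40 (40%) lost in seven weeks was on-treatment dropout in an augmentation trial in veterans, not loss after week 12. The 8-10% rejection rates also ignore the Bonferroni correction planned for secondary outcomes. If it applies here with a divisor of 4 or 5 (assumed), the rates are about 2.0-2.4% at 30% imputed and 2.9-3.5% at 40%, against corrected levels of 1.25% and 1.0%. These points stand: a false-positive rate near 10% should not be read as a prediction. The correction does nothing to the bias in the estimate itself.

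**Conclusion.** The point holds in a limited form. The general carry-forward rule is unsuited to the off-drug 24-week comparison, and as written it lets an on-treatment score stand for an off-drug one.

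With 30-40% imputed and the effect fully lost, both assumed, the range is 1.7 to 4.3 CAPS points, or roughly a quarter to two thirds of a standard error. At 10-20% imputed the bias is 0.6 to 2.1 points and the test is barely disturbed. If the effect persists in full off drug, the bias is zero.

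Only a secondary analysis is affected. The primary 12-week rule is stated consistently in both places, and nothing here bears on it. The change is worth making because the bias favours a claim of lasting benefit, which is the question the 24-week analysis exists to test.

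**What to change.** In Statistical Analysis:
- Restrict the general carry-forward sentence to data missing at 12 weeks.
- State that no on-treatment score is carried forward to week 24.
- Analyse week 24 with a likelihood-based repeated-measures model fitted to observed scores, with baseline score, treatment, visit and treatment-by-visit as terms and weeks 12 and 24 as outcomes. The week-12 score then informs the 24-week estimate without being assumed to persist off drug.

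The cost is analysis wording and a 24-week confidence interval somewhat wider than the carried-forward one, whose narrowness is partly artificial. The model assumes that missingness depends only on observed data. A patient with neither a week-12 nor a week-24 rating adds no outcome to it, so the number of such patients should be reported by arm. The primary analysis, sample size and treatment do not change.

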#### Wash-out phase

Patients will receive placebo pills and will be re-evaluated by the same psychiatrist one week after. Those having a significant improvement of the symptoms (a CGI-I score less than 3) will be excluded (avoiding premature placebo effects).

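### The intent-to-treat efficacy population is worded as patients who took topiramate, which literally leaves out the placebo arm; the wording must be corrected to cover both arms alike

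*Protocol article*

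**What the plan says.** The efficacy population is set in the second paragraph of the Statistical Analysis section: "Efficacy analyses will be performed in the intent-to-treat population of patients who received at least one dose of topiramate". The next sentence makes the change in CAPS total score the primary endpoint, measured "from baseline to the final visit at 12 weeks, which will be compared between treatment groups".

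Other sections bear on how this is read:

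- **Active treatment phase:** eligible patients "will be randomly assigned to receive either placebo or topiramate, in a 1:1 ratio". The pills are identical and staff are blinded.
- **Sample Size:** "The number of subjects calculated for the trial is 72, being 36 on each cell".
- **Statistical Analysis, first paragraph:** treatment group is the between-subject factor in the ANOVA. The intention-to-treat label appears here too, but only in connection with imputation: "For missing data we will use the last observation carried forward strategy for an intention-to-treat analysis".
- **Wash-out phase**, before randomisation: "Patients will receive placebo pills and will be re-evaluated by the same psychiatrist one week after".

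No other sentence in the article says who belongs to the efficacy population.

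**The concern.** An intent-to-treat set is fixed by assignment. This one is given that name but is defined by exposure to one arm's drug. A patient assigned to placebo, and treated as assigned, never meets the condition, so the definition conflicts with the comparison announced in the sentence after it.

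The primary analysis set decides who enters every efficacy test: the CAPS change, the response comparison and the secondary scales. If its only definition is wrong, someone has to decide later what was meant. The candidate repairs do not all give the same set. One of them requires a first dose in the topiramate arm and nothing in the placebo arm, so that comparable patients would be treated differently according to arm. In addition, whether a patient received topiramate cannot be known without the randomisation code, so membership under the printed rule cannot be settled while the trial is blind.

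**Working it through.** **Inputs.** 72 patients, 36 per arm (Sample Size; 2 × 36 = 72); 1:1 allocation (Active treatment phase); last observation carried forward for missing week-12 data (Statistical Analysis). The figure of 72 is used only to count patients. Whether it follows from the stated response rates and power is a separate question with no bearing here.

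**Step 1: apply each reading to the randomised arms.** Let *a* and *b* be the numbers randomised but never dosed in the topiramate and placebo arms. The article gives neither.

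| Reading | Topiramate | Placebo |
|---|---|---|
| Literal: must have taken topiramate | 36 − *a* | 0 |
| First-dose condition in the topiramate arm only | 36 − *a* | 36 |
| First dose of assigned study medication, both arms | 36 − *a* | 36 − *b* |
| All randomised | 36 | 36 |

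On the literal reading, at least 36 of 72 patients (50%) are out, including 36 of 36 on placebo (100%). The variance of a difference in means is proportional to 1/n_T + 1/n_P. With n_P = 0 it is undefined, so no two-group test exists.

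**Step 2: compare the workable readings.** If *a* = *b* = 0, the last three rows coincide and nothing is at stake beyond the wording. If *a* > 0, the second row differs from both symmetric ones.

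**Step 3: illustrate the size of the one-sided exclusion.** This rests on assumptions that the article does not supply:

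- *a* = *b*, taken as 1 or 2;
- a never-dosed patient has only a baseline score, which is carried forward as zero change;
- dosed patients improve by 52.7 CAPS points on topiramate and 42.0 on placebo, the reductions that the Background quotes from the earlier 12-week monotherapy trial.

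The differences in mean improvement are:

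- All randomised: (52.7 − 42.0) × (36 − *a*)/36
- Dosed in both arms: 52.7 − 42.0 = 10.70
- Topiramate-only condition: 52.7 − 42.0 × (36 − *a*)/36

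| *a* = *b* | All randomised | Dosed, both arms | Topiramate-only condition |
|---|---|---|---|
| 0 | 10.70 | 10.70 | 10.70 |
| 1 | 10.7 × 35/36 = 10.40 | 10.70 | 52.7 − 40.83 = 11.87 |
| 2 | 10.7 × 34/36 = 10.11 | 10.70 | 52.7 − 39.67 = 13.03 |

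Relative to all randomised patients, the one-sided rule shifts the difference by 52.7 × *a*/36: 1.46 points for one such patient and 2.93 for two. Under these assumptions the shift favours topiramate, because zero-change patients leave that arm and stay in the other.

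**Step 4: look for a sentence that repairs the rule.** The first paragraph's intention-to-treat label is attached to the handling of missing data and has no membership rule. It neither defines the set nor brings placebo patients back in. The conflict is therefore mainly within the second paragraph, and between that paragraph and the randomisation.

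**The case against.** The strongest reply is that nobody could misapply this sentence. The Active treatment phase section describes blinded medication for both arms in terms of the active drug's milligram doses, and the population sentence probably repeats that loose usage. CAPS change, response, completion and body weight are all compared between treatment groups. An analyst who applied the rule literally would find no control group and notice at once. With identical pills and blinded staff, failure to take a first dose should seldom depend on assignment, so any arm-specific exclusion would probably be small.

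Most of this stands. A reader might infer that the trial will be analysed without a control arm, or that the planned comparison cannot be made. The document does not support that: every other part of the plan presupposes two arms, and the loss of 36 of 72 patients follows only if the surrounding text is ignored. A reader might also infer that the investigators mean to exclude never-dosed patients from topiramate alone. Nothing in the article shows such an intention; the wording merely allows it.

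The reply does not show that the sentence is adequate. Recognising a slip does not settle which repair was meant: all randomised patients, all patients dosed after randomisation, or the one-sided set. Nor can the point be left to a separate analysis plan, because the article states a population here, and states it wrongly.

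**Conclusion.** The point holds as a wrongly worded definition of the primary efficacy population, and it must be corrected because no other definition exists in the article. Taken literally, it excludes every placebo patient and contradicts the between-group comparison and the 1:1 randomisation. This is very probably a drafting slip, so the literal loss measures the contradiction and does not forecast the analysis.

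The practical defect is narrower: it is unsettled whether never-dosed patients are excluded, and the text is open to an exclusion in one arm only. The size of that cannot be determined from the document. It is nil if every randomised patient takes a dose. The shift of roughly 1.5 CAPS points per never-dosed topiramate patient depends wholly on the assumptions listed in the working.

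**What to change.** Replace the population sentence with: *Efficacy analyses will include all randomised patients, analysed in the group to which they were assigned.* This matches the intention-to-treat label already in use.

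If a dosing condition is to be kept, use instead: *Efficacy analyses will include all randomised patients who received at least one post-randomisation dose of their assigned study medication (topiramate or placebo)*, applied identically to both arms. The words post-randomisation and assigned are needed. Every patient is given placebo pills in the wash-out week, so a condition naming only topiramate or placebo could be met before randomisation. State that wash-out pills do not count.

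Either version can be applied without unblinding. The cost is one sentence, with no change to the planned sample size or to trial conduct. It should be made before the randomisation code is opened.
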